**6.2.6. Proteomic profiling**

Proteomic profiling of collected blood samples for the advancement of the existing developed markers (to be used in this clinical trial) corresponding to Research Objective 2 and development of additional markers.

## 7. Data Analysis

### 7.1. Medical Device Code Name

- **Classification number:** A24500 (Grade 3)
- **Storage location:** 403, Health Care Innovation Park, Seoul National University Bundang Hospital, [name]
- **Product name:** MASTOCHECK
- **Product category:** in vitro diagnostic (IVD) software
- **Model name:** BM\_1BCM program
- **Ministry of Food and Drug Safety (MFDS) Approval Date:** 03 JAN 19

### 7.2. Data Analysis Procedure

Biomarkers are quantitatively analyzed by the proteomics analysis method for the blood collected through blood collection. The primary breast cancer screening model formula [Result = (0.604 X CAH1 concentration) + (7.7575 X NCHL1 concentration) - (0.523 X APOC1 concentration)] was established by using logistic regression analysis for the 3 proteins (Carbonic anhydrase 1; CAH 1, Neural cell adhesion molecule L1-like protein; NCHL1, Apo lipoprotein C-1; APOC1) finally selected through verification in the previous study. The quantitative analysis results of the obtained samples will be processed by the algorithm and the results will be compared to the results of the previous studies. An independent data management committee will be established to ensure efficiency and objectivity of data analysis and data analysis may include co-investigators and others who are not related to this study.

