**Figure 1. Mechanism of Multiple Reaction Monitoring (MRM)**

As a result, 11 out of 56 proteins showed significant difference in protein concentration between the normal group and breast cancer patient group with a P-value of <0.05. In particular, 3 proteins (carbonic anhydrase 1; CAH 1, neural cell adhesion molecule L1-like protein; NCHL1, apolipoprotein C-1; APOC1) showed a P-value of <0.001. The researchers determined the 3 proteins would be useful for breast cancer prediction and diagnosis and the proteins were finally selected as breast cancer biomarkers (11).

The final 3 proteins selected showed a P-value of <0.001 in all stages of breast cancer, including early stages (stage 1 and 2) as shown in Figure 1. The specificity for all breast cancer stages including early stages (stage 1 and 2) was the same as 78.75%, and the sensitivity was 78.75% for all stages and 80.64% for early stages (stage 1 and 2), respectively.

Therefore, the researchers at this investigational site utilized the 3 proteins (carbonic anhydrase 1; CAH 1, neural cell adhesion molecule L1-like protein; NCHL1, apolipoprotein C-1; APOC1) that were finally selected through verification, and established the following primary candidate formula for the early breast cancer screening model [Result = (0.604 X CAH1 concentration) + (7.7575 X NCHL1 concentration) - (0.523 X APOC1 concentration)] using logistic regression analysis (11).

In addition, the primary candidate formula established through verification was validated for the finally selected 3 proteins, using plasma samples from new donors whose samples were not included in the verification process (99 breast cancer patients and 99 normal subjects). As a result, as shown in Figure 1, sensitivity was 69.70% and specificity was 70.10% in all stages, while sensitivity was 77.21% and specificity was 68.13% in early breast cancer (stage 1 and 2) (11).

[figure not shown]

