**Table 2. Function of the three proteins**

However, the primary candidate formula established in the verification phase is not a formula derived from a quantitative method. While it is useful for comparison between groups such as patient group and normal subject (group), if the test is performed individually without comparison between groups, the decision cutoff value may change every time. Therefore, it was necessary to establish an early breast cancer screening model formula (algorithm) by establishing a test method as a quantitative method capable of individual evaluation rather than comparing between groups, and calculating the appropriate decision cutoff value. After improving the analysis method as a quantitative method, the researchers at this institution established a second formula (algorithm) for the early breast cancer screening model suitable for the quantitative method.

The samples used to develop the early breast cancer screening model formula (algorithm) were plasma samples stored in the biorepository of Lab of Breast Cancer Biology (LBCB), the Cancer Research Institute, Seoul National University College of Medicine.

In addition, to prevent bias in the analysis, the order of the samples used for the early breast cancer screening model formula was randomly mixed and then the samples were anonymized by being assigned non-descriptive numbers from 1 to 200. Sample donor information for early breast cancer and normal subjects was blinded to the researchers until analysis was completed. Utilizing the analyzed data, an early breast cancer screening model formula (algorithm) suitable for the quantitative method was established as a second algorithm through logistic regression analysis.

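### Section 7.2 prints only the first formula, which Section 1.1 calls unsuited to individual testing, and does not say which algorithm produces the primary endpoints

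*Protocol*

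**What the plan says.** Protocol Section 7.2 (Data Analysis Procedure) states that the markers will be quantified and then gives one formula, which begins "The primary breast cancer screening model formula [Result = (0.604 X CAH1 concentration) + (7.7575 X NCHL1 concentration" and ends by subtracting 0.523 times the APOC1 concentration. It attributes this to logistic regression in the previous study. It continues: "The quantitative analysis results of the obtained samples will be processed by the algorithm", and says that the results will be compared with those of previous studies. It mentions no other formula.

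Section 1.1 (Background) gives the same expression as the primary candidate formula from the verification work: "Result = (0.604 X CAH1 concentration) + (7.7575 X NCHL1 concentration) - (0.523 X APOC1 concentration)] using logistic regression analysis (11". After Table 2, the same section says that "the primary candidate formula established in the verification phase is not a formula derived from a quantitative method". It grants that the formula is useful for comparing groups, but adds that "if the test is performed individually without comparison between groups, the decision cutoff value may change every time". It then reports that, once the assay had been made quantitative, "the researchers at this institution established a second formula (algorithm) for the early breast cancer screening model suitable for the quantitative method".

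The synopsis and Section 2.1 make it the study's objective to evaluate a previously derived multi-marker algorithm together with its decision cutoff. The synopsis lists sensitivity, specificity and the ROC curve (concordance index) as the primary endpoints.

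**The concern.** In a diagnostic accuracy study the index test is the scoring rule plus the cutoff, so the analysis section has to leave no doubt about which rule is meant. Here the only rule written out in the analysis section is the one that the background sets aside for this use.

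This trial is also the setting in which Section 1.1 says the first formula is unreliable. Section 6.2.4 quantifies each sample against isotope-substituted standards. Sensitivity and specificity require each woman to be called positive or negative at a fixed threshold.

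All three primary endpoints are touched. If an analyst followed the printed formula, they would describe a test other than the one the protocol says was built for the quantitative assay. The comparison with earlier results required by 7.2, with Table 3 in Section 2.2 as the stated baseline, might then set two different tests side by side.

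**Working it through.** **1. Are the two formulas the same?**

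| Term | Section 1.1, first candidate formula | Section 7.2 |
|---|---|---|
| CAH1 | +0.604 | +0.604 |
| NCHL1 | +7.7575 | +7.7575 |
| APOC1 | −0.523 | −0.523 |

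They are identical. Section 7.2 drops the word *candidate*, so that *primary* can be read as *main*. In Section 1.1 it marks the first of two formulas.

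**2. What else in the protocol could identify the algorithm?**

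- Synopsis and Section 2.1: an algorithm and cutoff from previous studies, without saying which.
- Section 6.2.5: an algorithm that weights the markers, not identified.
- Section 7.1: MASTOCHECK, model BM_1BCM program, approved 03 JAN 19. The contents of the program are not described.
- Section 1.1: the second algorithm exists and suits the quantitative method. Its coefficients and cutoff are not printed, and it is not linked to BM_1BCM.

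No passage completes the chain from the wording of 7.2 to the second algorithm.

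**3. Which endpoints depend on what?** Write the score as S = b₁·CAH1 + b₂·NCHL1 + b₃·APOC1.

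- Sensitivity = P(S above the cutoff | cancer) and specificity = P(S not above the cutoff | no cancer). Both depend on the coefficients and on the cutoff.
- AUC = P(S of a cancer case exceeds S of a non-case), with ties counted as one half. It depends on the coefficients but needs no cutoff.

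Suppose, as an assumption for illustration, that a change of assay method multiplies the three measurements by k₁, k₂ and k₃. The old coefficients then give b₁k₁·CAH1 + b₂k₂·NCHL1 + b₃k₃·APOC1. If the three factors are equal, the ranking and hence the AUC are unchanged, and only the cutoff must move. If they differ, the relative weights change and the AUC can change too. The protocol gives no such factors.

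**4. Does the baseline identify the formula?** Table 3 gives sensitivity 67.0% and specificity 82.0%. With 100 cancers and 100 controls (group sizes inferred, not stated), its other figures reproduce exactly:

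- PPV = 67/(67 + 18) = 67/85 = 78.82%
- NPV = 82/(82 + 33) = 82/115 = 71.30%
- Accuracy = (67 + 82)/200 = 74.5%

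Section 1.1 reports for the first formula, all stages, 78.75%/78.75% in verification (80 versus 80) and 69.70%/70.10% in validation (99 versus 99). The latter gives an accuracy of (69.70 + 70.10)/2 = 69.9% with equal groups. The Table 3 pair is neither of these. The total of 200 matches the 200 samples that Section 1.1 describes for the second algorithm, but the protocol does not state that link.

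**5. Can an effect size be computed?** No. It would need both formulas and their cutoffs applied to the same samples. Only one formula and no cutoff are printed.

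**The case against.** The strongest reply is that 7.2 never says that the printed formula will be applied. That sentence is in the past tense and reads as history, and only the next one looks forward. In Section 1.1 the word *algorithm* goes with the new model and not with the first formula, so the forward-looking sentence can be read as meaning the second one. Section 7.1, directly above, names approved software, and the approval date precedes the planned start of 19 JUL 19. An analyst might simply run that program. This stands, and it limits the point to a contradiction in how the index test is specified.

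Four stronger readings are tempting and are not supported:

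- *The trial will evaluate the wrong test.* The past tense and Section 7.1 leave another reading open.
- *The printed formula is not the one in the approved software.* This is plausible, but no passage says which coefficients BM_1BCM holds.
- *Using the first formula costs about 12 points of specificity.* The difference 82.0 − 70.10 = 11.9 points compares two historical sample sets, possibly at different cutoffs, and sensitivity moves the other way (69.70% against 67.0%). Assuming 99 and 100 controls, the standard error is √(0.701·0.299/99 + 0.82·0.18/100) = 0.060, so the 95% interval runs from roughly 0 to 24 points. It measures nothing about this trial and should not be used.
- *The AUC fails for lack of a stable cutoff.* The AUC needs no cutoff and is affected only through the score.

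It can also be said that coefficients, cutoff and software version may sit in an analysis plan or device file that is not shown. That is fair, and their absence from the protocol is not the complaint. The complaint is that 7.2 prints the first formula, and no other, beside an unidentified algorithm.

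**Conclusion.** The point holds as a contradiction between Sections 7.2 and 1.1. Taken literally, the analysis section directs all three primary endpoints to a formula that the background describes as not quantitative in origin and without a dependable cutoff for individual use. Nothing else in the protocol settles which algorithm is meant.

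The coefficient match and the description in Section 1.1 are plain in the text and need no assumption. That the wrong test would actually be run is not established, and no numerical effect can be given. The point matters because it concerns the identity of the index test behind every primary endpoint, and because wording alone removes it.

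**What to change.** In Section 7.2:

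1. State that the algorithm applied to the study samples is the locked second algorithm, developed for the quantitative method, with its single pre-specified decision cutoff.
2. Identify it by the BM_1BCM software version, if that is what the program contains. The sponsor has to confirm this. A version reference is enough if the coefficients are confidential.
3. State that sensitivity, specificity and AUC are computed from that algorithm only.
4. Remove the first formula from 7.2, or mark it as historical and leave it in Section 1.1.

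This should be settled before sample information is disclosed for the statistical analysis (Section 8.2). The cost is protocol wording and whatever ethics review Section 10.1 requires for the amendment. It needs no further patients, samples or assays.

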#### <Protein quantitative analysis method>

- ① Instruments and tools used for quantitative analysis of 3 types of proteins

Instrument: LC-MS/MS (model name: API 5000, manufacturer: SCIEX, country of manufacture: Singapore, Korean medical device license number: Seoul, No. 10-1245)

Software: AB SCIEX's Analyst 1.6

Reagent: Commercially available stock solution reagent (DTT, IAA, Urea, Trypsin)

- ② Analyzer conditions

The pretreated plasma sample is expected to be quantitatively analyzed under the following LC-MS/MS conditions.

Analysis method: mass spectrometry (LC-MS/MS)

Detector: API 5000 Mass Spectrometer (Korean medical device license number: Seoul No. 10-1245)

MS/MS condition: Multiple Reaction Monitoring (MRM), Positive mode

## 8. Statistical Considerations

### 8.1. Sample Size Calculation

The researchers at this investigational site requested Seoul National University Hospital Medical Research Cooperation Center (MRCC) to calculate the number of study subjects. The correspondence with MRCC is quoted below:

We would like to confirm the diagnostic efficacy of the non-patient group for the breast cancer diagnostic index discovered by proteomics technique.

In order to estimate the sensitivity in the non-patient group, when the sensitivity value is  $p$ , the equation for calculating the number of subjects required to ensure their estimation accuracy to  $w\%$  (half the width of the 95% confidence interval) is as follows:

$$n = \frac{Z_{\alpha/2}^2 p(1-p)}{w^2}$$

| alpha/2 | Accuracy | Ratio | Number of subjects | Number of subjects considering the prevalence rate of 60% | Number of subjects considering the 10% dropout rate |
|---------|----------|-------|--------------------|-----------------------------------------------------------|-----------------------------------------------------|
| 0.025   | 0.06     | 0.60  | 257                | 429                                                       | 477                                                 |

**Table 4. Study subjects according to accuracy and ratio**

To calculate the number of subjects required for this study, a sensitivity of 60% is assumed by taking into account the sensitivity of 71.58% in the previous study. The number of subjects required to obtain estimation with 60% sensitivity and within 6% of precision is 257 for each group. Assuming the prevalence of 60%, the number of subjects required is calculated as a total of 429 subjects. In addition, if the 10% dropout rate is considered, a total of 477 subjects is required.

**\* After recruiting 300 subjects, the total number of patients to be recruited can be recalculated based on the events that occurred up to that point (calculation of the number of N-size by MRCC will be used as the reference).**

| Final Assessment Categories |                                               |                                                               |                                                                                                                                                                            |
|-----------------------------|-----------------------------------------------|---------------------------------------------------------------|----------------------------------------------------------------------------------------------------------------------------------------------------------------------------|
| Category                    |                                               | Management                                                    | Likelihood of cancer                                                                                                                                                       |
| 0                           | Need additional imaging or prior examinations | Recall for additional imaging and/or await prior examinations | n/a                                                                                                                                                                        |
| 1                           | Negative                                      | Routine screening                                             | Essentially 0%                                                                                                                                                             |
| 2                           | Benign                                        | Routine screening                                             | Essentially 0%                                                                                                                                                             |
| 3                           | Probably Benign                               | Short interval follow-up (6 month) or continued               | >0% but $\leq 2\%$                                                                                                                                                         |
| 4                           | Suspicious                                    | Tissue diagnosis                                              | 4a. low suspicion for malignancy (>2% to $\leq 10\%$ )
4b. moderate suspicion for malignancy (>10% to $\leq 50\%$ )
4c. high suspicion for malignancy (>50% to <95%) |
| 5                           | Highly suggestive of malignancy               | Tissue diagnosis                                              | $\geq 95\%$                                                                                                                                                                |
| 6                           | Known biopsy-proven                           | Surgical excision when clinically appropriate                 | n/a                                                                                                                                                                        |

Table 5. BI-RADS Assessment Categories

## 8.2. Randomization method

This study will not require blinding of subjects. Thus, only the investigators will be blinded to the information regarding blood samples. In order to prevent bias that may affect the test results during analysis, only the identification code of the sample will be displayed, and information on each sample will not be disclosed until statistical analysis.

## 8.3. Interim Analysis

Not applicable

## **9. Safety and Adverse Events**

The study will be conducted only with collected samples, and there will be no additional invasive testing methods or drug administration for patients. Therefore, it is judged that there will be very few possible adverse effects to the participants (patients).

## **10. Supporting Documentation and Operational Considerations**

### **10.1. Regulatory and Ethical Considerations**

- This study will be conducted in accordance with the protocol and with the following:
  - Declaration of Helsinki (revised in 2013)
  - Applicable ICH Good Clinical Practice (GCP) guidelines
  - Applicable laws and regulations
- The protocol, protocol amendments, ICF, and other relevant documents must be submitted to an IRB by the investigator and reviewed and approved by the IRB before the study is initiated.
- Any amendments to the protocol will require IRB/IEC approval before implementation of changes made to the study design, except for changes necessary to eliminate an immediate hazard to study participants.

### **10.2. Informed Consent Process**

- Investigator who will explain to study subjects and obtain consent: co-investigator of each participating institution
- Person who will provide consent: Study subject
- Duration between the process of explaining the study and the process of obtaining consent: Informed consent is planned to be obtained on the scheduled date of outpatient clinic visit for confirming the result of imaging examination (Informed consent process is expected to take approximately an hour).
- Method to minimize the possibility of coercion: Obtain consent from the patients voluntarily. (Explanation for obtaining consent should be made by the investigator (the principal investigator and co-investigator) specified in the clinical study protocol.
- Language used by the investigator in the process of explaining the research and obtaining consent: study information should be provided in terms that can be understood by the study subject using the study informed consent form
- Informed consent form provided to the study subject or lawfully authorized representative

### **10.3. Compensation plan for study subject**

- Compensation provided to study subjects: Financial compensation including round-trip transportation expenses
- After consent is given, the amount of compensation will be disclosed and paid to the subject promptly after the relevant visit (prevention of unfairness such as participation in research due to financial compensation by not mentioning compensation prior to consent)
- The compensation specified above are rewards for the subject consenting to the study and collecting blood. Therefore, it is not contingent on continued study participation. This study is terminated when statistical analysis is performed after blood collection and protein analysis in blood. The duration of the study is also short. Therefore, there is no need for the subject to continue to participate in the study.

#### **10.4. Recruitment strategy**

Among the patients who visited the investigational sites, patients who satisfy the inclusion criteria for breast imaging examination and able to provide informed consent for study participation after receiving study information from the medical staff (principal investigator or co-investigators) will be recruited as subjects.

#### **10.5. Personal information protection plan of study subjects**

Patient information in this hospital will be anonymized and managed from the time the sample is collected. Information that can identify individuals such as name and social security number will be redacted from clinical information. Only the analysis results will be shared and the raw data itself will not be disclosed. Information collected for research will be stored in an access-controlled physical location, in a file encrypted with a password. File access rights will be restricted to the principal investigator and co-investigator. When the research results are announced, the individual's identity will be announced in a form that cannot be identified, and case records after the end of the study will be kept separately by the principal investigator until thesis is published and approved, and it will be discarded under the guidance of the principal investigator according to Article 16 of the Enforcement Decree of the Personal Information Protection Act after storage for 3 years after the end of the study.

